#### Secondary analyses

A similar approach to the primary analysis will be adopted for the secondary outcomes, adjusting for baseline scores where appropriate.

#### Adverse events

Adverse events will be summarised descriptively. The frequency of each of the pre-specified adverse events will be reported by trial arm.

#### Health economic analysis

The cost-effectiveness of II versus care as usual for children and young people with PMLD will be evaluated over a 12-month period using a within-trial cost-utility analysis, which will assess a wide range of costs and health outcomes of II and report the results separately, so decision makers can form their own opinion on the most relevant results for their local context. The costing perspective of the NHS and Personal Social Services (NHS/PSS) and Education Services will be taken in the base case, with a set of scenario analyses conducted from both the NHS/PSS and the societal perspectives. Utilities collected via EQ-5D-Y (proxy version) will be used to generate quality-adjusted life years (QALYs), which will be taken in the base case. Other effectiveness outcomes that will be assessed include the QALYs measured by the CHU-9D (proxy version), CES and CCS (primary trial outcome). The cost-effectiveness results will be presented in terms of the incremental cost-effectiveness ratio (ICER) for II compared with care as usual. Health outcomes, resource use and cost data will be collected using parent/carer self-completed questionnaires (at baseline, 32 weeks and 52 weeks), and using the information recorded during the trial by teachers and interventionists.

The cost of delivering the II intervention will be estimated using a bottom-up approach, thereby incorporating the time spent by professionals training (for both trainers and trainees) and delivering the intervention (to plan and undertake II), as well as the costs of all associated resources and materials. Unit costs, obtained from established costing sources (e.g. NHS Reference costs, PSSRU), will be applied to each resource item to generate total cost estimates for each participating child/young person. Further costs feeding into the secondary analysis, such as societal perspective, will be collected to explore the impact of private expenditures (i.e. out-of-pocket medication expenditure, travel costs for appointments) and parent/carer time off work (for caring, attending appointments).

Mean within-trial estimates of costs and utilities will be generated using regression methods, adjusting for key covariates (including baseline utility), and allowing for any correlation between costs and utilities. Missing data patterns will be analysed to guide the multiple imputation methods used to deal with missing data [27]. Analyses will take an intention-to-treat approach, with findings presented in terms of mean costs and effects for both groups, as incremental cost-effectiveness ratios at 12 months. A non-parametric bootstrap re-sampling method will be used to produce confidence intervals around the cost and QALY differences and the ICER. The bootstrapped results will be presented in cost-effectiveness planes and cost-effectiveness acceptability curves [28]. A set of sensitivity analyses will be conducted to explore the robustness of the cost-effectiveness results. The NICE (2013) Guide to the Methods of Technology Appraisal will be followed wherever possible [29], and a pre-specified health economics analysis plan will be agreed with the trial’s independent groups and signed off by the chief investigators.

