### Sample size {19}

The primary outcome is the CCS at 32 weeks. A study utilising the CCS for communication skills of children with autism spectrum disorder who were minimally verbal [13] indicated that a 1-point increase in scores is a minimal clinically important difference (MCID). Assuming a MCID of one point on the CCS [13], a standard deviation of 2.08 [12], 90% power, 5% alpha, 20% loss to follow-up at the child/young person level, 10% drop out at the educational setting level, ICC = 0.09 (calculated from a similar trial published by the trial team, [22] and an average cluster size of 5, we would need to randomise 66 educational settings (330 children and young people). Sample size calculations were conducted in Stata v17 using the command clustersampsi. The Stata code used to determine the number of educational settings is given as follows:clustersampsi, mu1(0) mu2(1) sd1(2.08) sd2(2.08) m(4) rho(0.09) beta(0.9)with further adjustment to the number of educational settings to allow for up to 10% attrition.

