### Sequence generation: type of randomisation {21b}

Educational settings will be randomised to either receive II alongside usual care or usual care alone, using a 1:1 allocation ratio. Educational settings will be randomised via minimisation to ensure the best possible balance across educational setting characteristics within each group. A dedicated computer programme, MinimPY [23], will be used with the following minimisation factors:Age range of educational setting (primary age only (up to 11 years); non-primary (age 11 +); all age educational settings)Residential status of educational settings (residential; non-residential)Number of children and young people with PMLD (latest available data dichotomised at the median for recruited educational setting in the first batch to be randomised)Local authority region (East Midlands, East of England, London, North East, North West, Scotland or Wales, South East, South West, West Midlands, Yorkshire and Humber)

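### The planned bootstrap confidence interval around the ICER can be read only if nearly all replicates show a QALY gain; an interval for incremental net monetary benefit should replace it

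*Protocol article*

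**What the plan says.** The health economic analysis (protocol article, Statistical methods {27a}) makes the ICER the headline measure: "The cost-effectiveness results will be presented in terms of the incremental cost-effectiveness ratio (ICER) for II compared with care as usual". On uncertainty it states: "A non-parametric bootstrap re-sampling method will be used to produce confidence intervals around the cost and QALY differences and the ICER". The sentence after that puts the same bootstrap results on cost-effectiveness planes and acceptability curves.

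The section does not say how the ICER interval is formed from the replicates. It gives no condition under which that interval would be withheld, and it does not mention net monetary benefit. Detail is left to a separate document: "a pre-specified health economics analysis plan will be agreed with the trial’s independent groups and signed off by the chief investigators". That plan is not shown.

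**The concern.** The ICER is the cost difference divided by the QALY difference, and its meaning depends on the signs of both.

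- A negative ICER can mean that II is cheaper with more QALYs (dominant) or dearer with fewer QALYs (dominated).
- A positive ICER below the threshold is favourable if II gains QALYs at extra cost. It is unfavourable if II saves money and loses QALYs.

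An interval read from ordered ICER replicates therefore runs from worse to better value only if nearly all replicates have a positive QALY difference. Two other cases are possible:

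1. **Replicates straddle zero.** The ratios go to large values of both signs, and the limits typically become too wide to interpret.
2. **Nearly all replicates show a QALY loss at extra cost.** The ratios are nearly all negative, so the upper limit lies below any positive threshold although II is dominated.

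At stake is the error bar printed beside the headline economic result. Resampling whole settings would not cure this, because the problem lies in the ratio and not in the resampling.

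**Working it through.** **The plan's own figure.** The only design figure given is the sample size ({19}): "Assuming a MCID of one point on the CCS [13], a standard deviation of 2.08 [12], 90% power, 5% alpha", with "20% loss to follow-up at the child/young person level, 10% drop out at the educational setting level". The code uses 4 children per setting and an ICC of 0.09.

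- Per arm without clustering: 2 × (2.08 × (1.960 + 1.282))² = 90.9, so 91.
- Design effect: 1 + 3 × 0.09 = 1.27.
- Settings per arm: 90.9 × 1.27 / 4 = 28.9, so 29. Then 29 / 0.9 = 32.2, so 33.
- Total: 66 settings, × 5 = 330 children. The stated figure reproduces.

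**Assumed inputs.** The documents give no cost, QALY SD or threshold. The assumptions are:

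- QALY SD 0.14 to 0.27.
- 240 analysed children (about 60 settings × 4, so 120 per arm).
- The design effect of 1.27 carried over from the primary outcome.
- Extra cost £500 (SE £200) to £1,000 (SE £400).
- Threshold £20,000 per QALY.
- Independent normal differences and a percentile interval.

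The SE of the QALY difference is SD × √(2 × 1.27 / 120) = SD × 0.1455. This gives 0.020 at SD 0.14, 0.029 at SD 0.20 and 0.039 at SD 0.27, so a range of 0.02 to 0.04.

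**How often replicates straddle zero.** Take straddling to mean more than 2.5% of replicates on each side. With true difference d and standard error s, the probability is Φ(1.96 − d/s) − Φ(−1.96 − d/s).

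| True QALY difference | s = 0.02 | s = 0.03 | s = 0.04 |
|---|---|---|---|
| 0 | 0.95 | 0.95 | 0.95 |
| 0.02 | 0.83 | 0.90 | 0.92 |
| 0.05 | 0.29 | 0.62 | 0.76 |

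Simulation agrees: about 82-95% for true differences of 0 to 0.02.

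**What the ordered ICERs then show.** These are 400,000 replicates centred on the stated differences, with assumed SEs of 0.02 QALY and £500, and a £20,000 threshold. INB is incremental net monetary benefit, £20,000 × QALY difference − cost difference.

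| QALY, cost difference | Ordered ICER interval (£) | P(ICER < £20,000) | P(INB > 0) | INB interval (£) |
|---|---|---|---|---|
| +0.08, +£1,000 | 252 to 32,578 | 0.825 | 0.825 | −652 to 1,852 |
| +0.02, +£1,000 | −452,009 to 509,027 | 0.329 | 0.174 | −1,858 to 656 |
| −0.02, +£1,000 | −516,326 to 453,389 | 0.848 | 0.014 | −2,658 to −145 |
| −0.02, −£1,000 | −456,937 to 518,585 | 0.329 | 0.825 | −654 to 1,859 |

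In the first row nearly all replicates show a QALY gain, and the ICER ordering agrees with net benefit. In the other three it does not, and the limits are about half a million pounds either way.

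**When the upper limit falls below £20,000 although II is not cost-effective.** These are simulated trials (2,000 trials × 2,000 replicates) across the assumed SE and cost range. The upper limit was below £20,000 in 8-18% of trials at a true loss of 0.02 QALY, and in 19-54% at a true loss of 0.04.

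Most of this comes from the second case, where at least 97.5% of replicates show a loss. Its probability is Φ(−1.96 − d/s):

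- d = −0.02: 0.17, 0.10 and 0.07 for s = 0.02, 0.03 and 0.04.
- d = −0.04: 0.52, 0.27 and 0.17.

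At s = 0.03 with £500 (SE £200), splitting the trials directly gave 0.106 of 0.127 at a loss of 0.02, and 0.26 of 0.29 at a loss of 0.04. If II does no harm the rate is near nominal: 0.035 at a true difference of 0 and 0.026 at +0.02, against 0.025.

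**The case against.** Several points on the other side carry weight.

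- **The method of forming the interval is not stated.** The article says only that it is a non-parametric bootstrap, and the health economics analysis plan may specify something else or restrict its use. This stands as a limit on certainty. However, the commitment to an ICER interval is explicit and unconditional, so a plan consistent with it would carry the problem forward.
- **A reader might infer that the economic analysis cannot show whether II is cost-effective.** The documents do not support that. The cost and QALY difference intervals, the plane and the acceptability curves are all planned. The curve gives the probability of positive net benefit at each threshold from the same replicates.
- **A reader might also infer that mixing of opposite quadrants makes the interval look favourable in up to 54% of trials.** That is not supported either. Those figures arise only if II truly loses 0.02 to 0.04 QALY, and the protocol anticipates no substantial risk. Most of those trials lie on the loss side, where the QALY interval printed alongside would be at or below zero and the result would be reported as dominated. When replicates straddle zero, the interval is usually visibly uninformative and not deceptively favourable.
- **All economic inputs are assumed.** The ICC for QALYs is borrowed from the primary outcome. Adjustment for baseline utility and correlation between costs and QALYs, both planned, are not modelled. The percentages could shift; the ordering argument does not depend on them.

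**Conclusion.** The point holds in a limited form. The article commits to an interval on the ICER that can be read as a range of value for money only if nearly all replicates show a QALY gain, and that cannot be known beforehand. Under the assumed SEs, a true difference of 0 to 0.02 QALY leaves replicates on both sides of zero in about 82-95% of trials, and the limits then typically carry no usable information. A clear QALY loss at extra cost gives limits below any threshold for a dominated intervention. With a clear gain there is no distortion. This is a defect in one reported quantity beside the headline result and does not invalidate the economic evaluation. The sizes rest on assumed costs, QALY SDs, threshold and a percentile interval, none of which the documents state.

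**What to change.** In the health economics analysis plan, replace the ICER interval with a bootstrap 95% confidence interval for incremental net monetary benefit at the thresholds used for the decision, computed from the same replicates. Report the ICER as a point estimate, or state dominance where it applies. Keep the cost and QALY difference intervals, the planes and the acceptability curves as planned.

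The cost is a wording change and one computed line per threshold, with no new data. The article says the plan will be developed ahead of the analysis, and final follow-up is due in December 2026. The one downside is that net benefit must be shown at stated threshold values, which the plan would then have to name.

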### Who will be included in each analysis {27b}

The analysis will be undertaken according to the principles of intention to treat (ITT). All randomised participants, with the exception of those that have fully withdrawn and have asked for their data to be removed from the dataset, will be included in the analysis.

### How missing data will be handled in the analysis {27c}

We will assess the impact of missing data on the study results. Case and item missing data will be examined, and multiple imputation methods may be used to reduce bias due to any missing responses in the analyses. Where appropriate, modelling methods that generate robust standard errors in the presence of missing data will be considered.

### Methods for additional analyses (e.g. subgroup analyses) {27d}

A subgroup analysis will consider whether there is evidence of a differential intervention effect depending on the age of the child and/or young person (primary vs non-primary age provision). This will be assessed by repeating the primary analysis but including an indicator variable for whether the child and/or young person is attending a primary educational setting or a non-primary educational setting at baseline as a covariate plus an interaction term between treatment allocation and age provision.

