### Characteristics of the people who are needed for the trial

**Table Taba:** 

Characteristic	The people we would expect to see included
Age	Children and young people aged between 3 and 25 years
Sex	Data will be collected from parent/carers regarding their children’s biological sex. Parent/carers will be asked to select from the following options: • Male • Female • Other
Gender	Given the population of children and young people with profound and multiple learning disabilities, only data regarding biological sex as described above will be collected
Race, ethnicity and ancestry	No restrictions will be placed on eligibility on the basis of race, ethnicity or ancestry. Parent/carers will be asked to describe their children’s ethnicity by selecting from the following categories: • White • Asian/Asian British • Black/Black British/Caribbean or African • Mixed or multiple ethnic groups • Other ethnic group
Socioeconomic status	We anticipate families from a range of socioeconomic backgrounds. Initially, we planned to capture data around parent/carer employment, education and training; however, after taking guidance from our PPIE group, these were removed to reduce the length of the questionnaire, and because they were viewed as unduly intrusive. We will collect data on whether or not parent/carer providing data are currently in employment, education or training, but nothing further
Geographic location	Recruitment will take place across Great Britain (England, Wales and Scotland). No restrictions will be in place with regard to geographical location. We anticipate a national spread of participants
Other characteristics relevant to the trial	No additional characteristics

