#### Primary analysis

The primary analysis will compare the optimal CCS score between groups using a covariance pattern mixed linear model, incorporating all post-randomisation time points (32 and 52 weeks). The model will adjust for minimisation factors, baseline optimal CCS score, time, treatment arm, treatment-by-time interaction and other relevant baseline covariates as fixed effects, with educational setting and child/young person as random effects to account for the clustering by setting and repeated observations per participant. The correlation of observations within participants over time will be modelled by a covariance structure. The Akaike information criterion will be used to compare models specifying different covariance structures (smaller values preferred). Model assumptions will be checked, and if they are in doubt, the data will be transformed prior to analysis. The treatment effect overall and at both time points (32- and 52 weeks) will be extracted in the form of an adjusted mean difference, 95% confidence interval and *p* value. The primary timepoint of interest is 32 weeks post-randomisation.

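### The age subgroup analysis uses a two-level setting type that has no defined place for pupils in all-age settings; the child's own age should define it

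*Protocol article*

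**What the plan says.** The section on additional analyses {27d} sets the question as a "differential intervention effect depending on the age of the child and/or young person (primary vs non-primary age provision"). It then fixes the variable by "including an indicator variable for whether the child and/or young person is attending a primary educational setting or a non-primary educational setting at baseline", with an interaction between allocation and age provision, in a repeat of the primary analysis.

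The section on type of randomisation {21b} classifies settings in three ways for minimisation: "primary age only (up to 11 years); non-primary (age 11 +); all age educational settings".

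Participants are "Children and young people aged between 3 and 25 years". The primary model, which the subgroup analysis repeats, already carries the three-level age range: "The model will adjust for minimisation factors, baseline optimal CCS score, time, treatment arm, treatment-by-time interaction". The article does not say how pupils in all-age settings are to be coded in the two-level indicator.

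**The concern.** The question concerns the child, but the variable describes the setting. The two agree when a setting takes only primary-age pupils or only older ones. They part company in an all-age setting, which on the trial's own classification is neither. If such a setting is counted as non-primary, a 5-year-old there is analysed with the older group; if it is counted as primary, a 20-year-old is analysed with the younger group. Either way the two groups become more alike in age than their labels suggest, and a real difference in effect between younger and older children is diluted.

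All-age settings are a planned minimisation category, so this is not a remote case. A null interaction would then be hard to read: it could mean no effect modification by age, or only that the groups were mixed.

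**Working it through.** **The plan's own figure.** No figure is given for the subgroup analysis. The overall sample size reproduces. The inputs, from Sample size {19}, are a 1-point difference, SD 2.08, 90% power, 5% alpha (taken as two-sided), 4 children analysed per setting, ICC 0.09 and 10% loss of settings.

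- Per arm, unclustered: 2 × (2.08 × (1.960 + 1.282))² = 90.9
- Design effect: 1 + 3 × 0.09 = 1.27, giving 115.5 per arm
- Settings per arm: 115.5 / 4 = 28.9, so 29; 29 / 0.9 = 32.2, so 33
- Total: 66 settings, × 5 = 330 children

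The point therefore does not rest on a faulty sample size.

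**The definitions side by side.** Section {21b} has three setting types and section {27d} has two. Primary-only and 11+ settings map directly. All-age settings have no counterpart, and no rule supplies one.

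**Dilution if all-age settings are pooled with non-primary.** Let q be the share of children in all-age settings and p the share of those who are of primary age. Assume that the remaining children divide evenly between primary-only and 11+ settings, that the effect differs by age group only, and that children count equally.

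- Share coded non-primary: (1 − q)/2 + q = (1 + q)/2
- Primary-age share within that group: f = qp / ((1 + q)/2) = 2qp/(1 + q)
- The coded non-primary effect is f × (younger effect) + (1 − f) × (older effect). The coded primary group contains only younger children. The contrast is therefore (1 − f) times the true age interaction, and the loss is f.

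| q | p = 0.3 | p = 0.5 | p = 0.7 |
|---|---|---|---|
| 0.2 | 10.0% | 16.7% | 23.3% |
| 0.4 | 17.1% | 28.6% | 40.0% |
| 0.6 | 22.5% | 37.5% | 52.5% |

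For example, q = 0.2 and p = 0.3 gives 0.12/1.2 = 10%; q = 0.6 and p = 0.7 gives 0.84/1.6 = 52.5%.

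Pooling with primary instead replaces p by 1 − p, so the same grid of assumptions gives the same range. With q = 0 the loss is zero.

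**How strong the analysis is to begin with.** Take about 60 settings (66 × 0.9 = 59.4), 4 children each, and four equal cells of 60 children. The standard error of a setting-level interaction is √(4 × 2.08² × 1.27 / 60) = 0.605. Power for a true 1-point interaction is then about 38%, before any dilution.

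**The case against.** The strongest reply is that section {27d} does not say its indicator is the minimisation factor. It is worded per child and speaks of age provision, so a pupil in the primary phase of an all-age school might be meant to count as primary. Coding rules also commonly belong in the SAP, which is promised and not shown. The analysis is exploratory, with low power under any coding, and every share behind the dilution figures is assumed.

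Much of this stands. The figures are illustrative, and the intended coding may be sensible. But the operative words refer to attending a primary or non-primary educational setting, and the article elsewhere names a third type of setting. That is more than omitted detail: the variable as written does not match the question as written, and an SAP that copied it would inherit the mismatch.

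A reader might infer three stronger things that the document does not support:

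- **That age is not tested at all.** In settings restricted to one age band the indicator is a fair proxy for being below or above about 11.
- **That pupils in all-age settings will be dropped.** The section on who is analysed {27b} includes every randomised participant except those who fully withdrew and asked for their data to be removed, and {27d} repeats the primary analysis. Exclusion would contradict both, so a loss of precision from dropping settings is not a consequence of the plan.
- **That the model fails because a setting-level indicator duplicates the three-level factor.** Only the indicator's main effect is redundant; the interaction remains estimable.

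**Conclusion.** The point holds, confined to all-age settings. The subgroup variable is a setting type that leaves those pupils without a defined place, while the stated question is about the child's age. Pooling all-age settings into one level would shrink the interaction by about 10% to 53%, if 20% to 60% of children attend them, 30% to 70% of those are of primary age, and the rest divide evenly. A smaller all-age share would mean a smaller loss, and the article does not give the real share. The primary analysis, sample size and trial conduct are unaffected. The correction is worth making before the analysis because this is the only subgroup analysis that the article names.

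**What to change.** Define the subgroup by each child's own age at baseline, primary age versus older, with a single cut. State on which side age 11 falls, because the setting categories in {21b} meet there: one runs up to 11 and the other starts at 11. Fit the treatment-by-age-group interaction in the primary model. Keep the three-level setting age range only as a minimisation covariate. Continuous age may be added as a supporting analysis.

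The cost is a change of wording in the SAP and a short protocol clarification, made before the analysis. Age is an eligibility criterion and decides the consent route at 16, so it should be known for every participant. It does not appear in the article's list of other baseline variables, so the sponsor should confirm that age at baseline reaches the analysis dataset.
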